## Abstract

**Backgrounds:**

Glomerular diseases, a set of debilitating and complex disease entities, are related to mortality and morbidity. To gain insight into pathophysiology and novel treatment targets of glomerular disease, various types of biospecimens linked to deep clinical phenotyping including clinical information, digital pathology, and well-defined outcomes are required. We provide the rationale and design of the KOrea Renal biobank NEtwoRk System TOward Next-generation analysis (KORNERSTONE).

**Methods:**

The KORNERSTONE, which has been initiated by Korea Centres for Disease Control and Prevention, is designed as a multi-centre, prospective cohort study and biobank for glomerular diseases. Clinical data, questionnaires will be collected at the time of kidney biopsy and subsequently every 1 year after kidney biopsy. All of the clinical data will be extracted from the electrical health record and automatically uploaded to the web-based database. High-quality digital pathologies are obtained and connected in the database. Various types of biospecimens are collected at baseline and during follow-up: serum, urine, buffy coat, stool, glomerular complementary DNA (cDNA), tubulointerstitial cDNA. All data and biospecimens are processed and stored in a standardised manner. The primary outcomes are mortality and end-stage renal disease. The secondary outcomes will be deterioration renal function, remission of proteinuria, cardiovascular events and quality of life.

**Discussion:**

Ethical approval has been obtained from the institutional review board of each participating centre and ethics oversight committee. The KORNERSTONE is designed to deliver pioneer insights into glomerular diseases. The study design allows comprehensive, integrated and high-quality data collection on baseline laboratory findings, clinical outcomes including administrative data and digital pathologic images. This may provide various biospecimens and information to many researchers, establish the rationale for future more individualised treatment strategies for glomerular diseases.

**Trial registration:**

NCT03929887.

## Background

The prevalences of chronic kidney disease (CKD) and end-stage renal disease (ESRD) are continuously increasing around the world. Recent evidence indicates that the number of incident ESRD patients due to glomerular diseases is increasing [1, 2], and many additional ESRD cases are expected to have been attributed to glomerular diseases, considering the cases that have not been confirmed by kidney biopsy. However, the discovery of pathognomonic biomarkers and disease-specific therapeutic targets for glomerular diseases is limited.

To better understand the pathophysiology, biomarkers, and treatment targets of glomerular diseases and ultimately to improve clinical outcomes, it is imperative to translate and integrate research with various types of biospecimen linked to deep clinical phenotyping, including clinical information, self-questionnaires, digital pathology and outcomes from the electronic health record (EHR) and administrative data. A significant additional number of kidney disease cohorts were established through several international consortiums. The C-PROBE, [3] ERCB cohort [4] with CKD patients, and Nephrotic Syndrome Study Network (NEPTUNE) cohort [5] for patients with nephrotic syndrome were started in approximately 2010, and these cohorts are relatively small. Recently, large-scale genomics consortia, including CKDGen [6] and EURenOmics, [7] have been activated in the United States and Europe. However, these cohorts are not sufficient to support data for Asians. To that end, a multicentre prospective cohort based on deep clinical phenotypes, biospecimens, and digital pathology has been established in Korea, the ‘KORNERSTONE’, which is supported by the Korea Centers for Disease Control and Prevention (KCDC).

The objectives of the KORNERSTONE are as follows: 1) establish a collaborative, innovative deep clinical phenotype-based investigational infrastructure to carry out clinical and translational studies of glomerular disease; 2) perform a longitudinal observational cohort study of patients with biopsy-proven glomerular diseases; and 3) gain insight into the pathophysiology, natural history and novel treatment targets of glomerular diseases. In the present paper, we report the KORNERSTONE design and methods in detail.

## Methods/design

### Ethics statements

The basic protocol of this study was approved by the ethics committee of each participating centre, including the institutional review boards of Seoul National University (1404–117-575), Keimyung University Dongsan Hospital (DSMC 2019–04–015-001), Chung-Ang University (1942–005-369), Severance Hospital (2019–0463-001), Boramae Medical Center (L-2019-126), and Kangwon National University Hospital (KUNH-2019-05-009). Additionally, the ethics oversight committee of the KORNERSTONE reviewed the design and protocols of this study. All of the ethical issues regarding the plans of the KORNERSTONE cohort study will be supervised by this committee.

### Study design and population

The KORNERSTONE is a prospective multicentre observational biobank, databank and digital pathology repository of patients with glomerular disease in Korea (NCT 03929887 at http://www.clinicaltrials.gov). Nephrologists working in six clinical centres in the major university-affiliated hospitals, pathologists, and paediatricians are participating in this study. Among the six clinical centres, four centres are located in the metropolitan city of Seoul, one is in the southern area, and the last centre is in northeastern Korea.

Patients suspected of glomerular diseases who received kidney biopsy in participating university medical centres are eligible for inclusion in the KORNERSTONE. Patients who previously received a kidney transplant will be excluded. This study will enrol 3000 children (age < 18 years) and adults. Eligible participants will be screened at the inpatient or outpatient clinic of the department of nephrology or paediatrics of each participating hospital. Participants who pass an initial screening and agree to participate will provide written informed consent during their visit. Parents of all children, and children themselves if age more than 6 years, provided written informed consent. Informed consent includes utilization, collection, and provision of demographics, clinical information, and social security number for the linkage of administrative data and biospecimens. When a participant wants to withdraw from the KORNERSTONE, all stored biospecimens and data will be destroyed or deleted. All of the laboratory data, self-questionnaires and biospecimens will be collected at the time of kidney biopsy for the baseline information (Table 1). Patients or the public were not involved in the design, or conduct, or reporting, or dissemination plans of our research.

**Table 1 Tab1:** List of clinical information and biospecimens in the KORNERSTONE

Parameters	Detailed information	Screening	Baseline	1 Y	2 Y	3 Y	4 Y	5 Y	Improvement or deterioration of clinical outcomes	Hard outcomes (ESRD, CV outcomes)
**Informed consent**		O								
**Demographic information**		O								
**Medical history**		O								
**Medications**	Hypertensive medications		O	O	O	O	O	O	O	O
	Immunosuppressant		O	O	O	O	O	O	O	O
**Questionnaires**	Health questionnaires (including smoking)		O	O	O	O	O	O	O	O
	KDQOL-SF version 1.3 questionnaires		O	O	O	O	O	O	O	O
	Semi-food frequency questionnaires		O	O	O	O	O	O	O	O
	PedsQL 4.0 Generic Core Scales (Children)		O							O
**Anthropometry**	Height, weight		O	O	O	O	O	O		O
	Blood pressure		O	O	O	O	O	O		O
**Blood laboratory findings**	CBC (white blood cell count, platelet, haemoglobin)		O	O	O	O	O	O	O	O
	Chemistry (calcium, phosphorus, glucose, blood urea nitrogen, uric acid, total protein, albumin, total bilirubin, alkaline phosphatase, AST, ALT)		O	O	O	O	O	O	O	O
	IDMS-traceable Cr, eGFR		O	O	O	O	O	O	O	O
	Lipid panel (total cholesterol, triglyceride, high-density lipoprotein, low density lipoprotein)		O	O	O	O	O	O	O	O
	Electrolyte panel (sodium, potassium, chloride)		O	O	O	O	O	O	O	O
	Total CO_2_		O	O	O	O	O	O	O	O
	C-reactive protein		O	O	O	O	O	O	O	O
	Serology (HBsAg, HBsAb, Anti-HCV, HIV, VDRL)		O							
	Anti-dsDNA, FANA, FANA titre, ANCA, PR3, MPO		O							
	Complement 3, 4		O							
	ASO, rheumatoid factor, Cryoglobulin		O							
**Urine laboratory findings**	Random urine protein		O	O	O	O	O	O	O	O
	Random urine microalbumin		O	O	O	O	O	O	O	O
	Random urine creatinine		O	O	O	O	O	O	O	O
	Urinalysis protein		O	O	O	O	O	O	O	O
	Urinalysis RBC		O	O	O	O	O	O	O	O
**Kidney biopsy**	Biopsy results and images including LM, IF and EM		O							
	Report of diagnosis		O							
	Total number of glomeruli		O							
	Total number of global sclerosis/segmental sclerosis/crescent		O							
**Biospecimens**	Serum/plasma/buffy coat/genomic DNA sample		O	O	O	O	O	O	O	O
	Urine sample		O	O	O	O	O	O	O	O
	Stool sample		O							
	cDNA from glomeruli and tubules in micro-dissected kidney biopsy tissues		O							

*CBC* complete blood count; *KDQOL-SF* Kidney Disease-Quality of Life Short Form; *PedsQL* Pediatric Quality of Life Inventory; *AST* aspartate aminotransferase; *ALT* alanine aminotransferase; *HCV* hepatitis C virus; *HIV* human immunodeficiency virus; *VDRL* veneral disease research laboratory test; *FANA* fluorescent antinuclear antibody; *MPO* myeloperoxidase; *ASO* antistreptolysin O; *RBC* red blood cell; *LM* light microscopy; *IF* immunofluorescent; *EM* electron microscopy; *IDMS* isotope dilution mass spectrometry; *Cr* creatinine; *eGFR* estimated glomerular filtration rate; *Y* year

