### Clinical, patient-oriented outcomes and follow-up

After enrolment, all of the participants will be assessed for whether they reach clinical endpoints each time they visit the outpatient clinic. The clinical endpoints of this study were divided into two categories: 1) deterioration of clinical outcomes was defined by doubling of serum Cr or decrease in estimated glomerular filtration rate (eGFR) by more than 30%, and 2) improvement of clinical outcomes was defined by the remission of glomerulonephritis and proteinuria < 0.3 g/day. Other hard outcomes were defined by ESRD, cardiovascular events, and death. The patients who have proteinuria < 0.3 g/day at baseline have no improvement in clinical outcomes.

Whether the enrolled patients reached each clinical endpoint will be confirmed by the EHR. If the participant displays deterioration, improvement of clinical outcomes, ESRD or cardiovascular events, laboratory findings, urinalysis, and biospecimens, including serum, plasma, buffy coat, and urine, will be collected from the participants. Stools will be collected at baseline only. Additionally, the same information and biospecimens will be collected from the participants at least once per year.

In addition, the patient-oriented outcome will be secured by age-appropriate questionnaires. These outcomes will include symptoms from the patient’s perspective, functional status, nutritional status and health-related quality of life. The questionnaires will be collected every year.

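### Table 1 gives the children's quality-of-life questionnaire (PedsQL) at none of the five annual visits, although the text has questionnaires collected every year

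*Protocol article*

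**What the plan says.** Quality of life is a declared secondary outcome. The abstract's Methods paragraph states: "The secondary outcomes will be deterioration renal function, remission of proteinuria, cardiovascular events and quality of life". Children are part of the cohort, though their number is not given: "This study will enrol 3000 children (age < 18 years) and adults" (Study design and population).

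The text sets a yearly schedule in two places:

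- Abstract, Methods: "Clinical data, questionnaires will be collected at the time of kidney biopsy and subsequently every 1 year after kidney biopsy".
- Clinical, patient-oriented outcomes and follow-up: "the patient-oriented outcome will be secured by age-appropriate questionnaires". Health-related quality of life is listed among these outcomes, and the paragraph ends: "The questionnaires will be collected every year".

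Table 1 sets a different schedule for one instrument. The row "PedsQL 4.0 Generic Core Scales (Children" is marked at Baseline and in the column headed "Hard outcomes (ESRD, CV outcomes", and nowhere else. The row "KDQOL-SF version 1.3 questionnaires" is marked at Baseline, at all five years and in both event columns. The health and food-frequency questionnaires are marked in the same way.

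**The concern.** PedsQL is the only instrument in the article labelled for children. Table 1 is also the only place that says when it is given, because the section on the electronic health record and questionnaires names the KDQOL-SF and does not mention PedsQL. A site that works from the table would give PedsQL once at biopsy and then only to a child with ESRD or a cardiovascular event.

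That makes measurement depend on outcome. Children who stay stable, remit or lose function without reaching a hard outcome would contribute a baseline score and nothing more. Any observed change on PedsQL would be change among children selected for a bad course, measured at the event and not at a planned time. If some centres follow the table and others the text, the missing data would also differ by centre. The linked records described in the article supply deaths, ESRD, diagnoses and prescriptions, but not patient-reported scores, so an assessment not made at the time is lost.

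**Working it through.** No power or sample-size figure in the article underlies this point, so there is no planned number to reproduce. The check is a cell-by-cell reading of Table 1 against the text, followed by an illustration of scale.

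**1. Are the blanks real?** The header of Table 1 has 11 fields, and so does the PedsQL row. The row is therefore not shifted or cut off, and the empty cells are empty in the table.

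| Source | Baseline | Years 1–5 | Improvement or deterioration | Hard outcomes |
|---|---|---|---|---|
| Table 1, PedsQL | yes | 0 of 5 | no | yes |
| Table 1, KDQOL-SF | yes | 5 of 5 | yes | yes |
| Text, age-appropriate questionnaires | yes (abstract) | every year | not stated | not stated |

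**2. Does the pattern occur elsewhere in the table?** No. Every other row marked under hard outcomes is also marked at all five years. Every other row without annual marks has no hard-outcome mark either.

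**3. Is an exception stated?** No. The follow-up section does state one for stool, which is taken only at baseline. It has no such sentence for PedsQL.

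**4. What does Table 1 leave estimable?** Let h be the proportion of children who reach ESRD or a cardiovascular event within 5 years. Let D1 be the mean PedsQL change in those children and D0 the mean change in the rest.

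- Mean change in all children = h × D1 + (1 − h) × D0.
- Table 1 yields data on D1 only.
- Using D1 for all children gives an error of D1 − [h × D1 + (1 − h) × D0] = (1 − h) × (D1 − D0).

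Nothing collected under Table 1 informs D0, so neither the size nor the sign of D1 − D0 can be checked.

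**5. Illustration of 1 − h, the share of children with no PedsQL after baseline.** The article gives no paediatric event rate, so h is an assumption:

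- h = 0.05: 1 − 0.05 = 0.95
- h = 0.12: 1 − 0.12 = 0.88 (the 5-year ESRD rate in Table 2, a planning rate not specific to children; cardiovascular events ignored)
- h = 0.20: 1 − 0.20 = 0.80

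The range is 80% to 95%. It refers to PedsQL only, and it ignores children who turn 18 during follow-up.

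**The case against.** The strongest counter-argument concerns what is lost. A reader might infer from Table 1 that children have no quality-of-life data at all after baseline unless they reach a hard outcome. The article does not support that. The KDQOL-SF row is yearly and carries no adults-only label. The section on questionnaires has participants complete the KDQOL-SF under the description age-appropriate and excludes no children. The health questionnaire is yearly too. Children may therefore have yearly quality-of-life scores on another instrument. This limits the point to PedsQL but does not remove it: KDQOL-SF scores would not supply the missing follow-up on the one scale designated for children.

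A second argument is that the text may govern and that the row may simply lack marks by oversight. That is plausible, and nothing in the article shows that measurement by outcome was intended. The harm is therefore conditional on sites following the table. The contradiction stands either way, because the article does not say which of the two prevails.

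Three smaller objections also hold. The abstract says only questionnaires; the link between age-appropriate instruments and yearly collection is made in the follow-up section alone. The text does not call for questionnaires at improvement or deterioration: its list for those events covers laboratory findings, urinalysis and biospecimens, and the anthropometry rows are blank in that column as well. Finally, mortality and ESRD, the primary outcomes, are obtained from health records and administrative data and do not depend on any questionnaire.

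**Conclusion.** The point holds as an internal contradiction about one instrument. Table 1 schedules PedsQL at 0 of 5 annual visits, and the follow-up section and the abstract have questionnaires collected every year. The figure 0 of 5 is read directly from the table and needs no assumption.

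If sites follow Table 1, PedsQL after baseline exists only for children with ESRD or a cardiovascular event. Change on that scale is then not estimable for other children and is conditional on a bad outcome. The range of 80% to 95% of children without PedsQL follow-up rests on assumed hard-outcome rates of 20% to 5%; the conclusion does not depend on it.

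The point should be corrected, because the lost data cannot be recovered and concern a declared secondary outcome. It does not threaten the study's main purpose: the primary outcomes are untouched, and the point affects one scale in a subgroup of unstated size.

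**What to change.** Mark PedsQL at years 1 to 5 in Table 1, so that the table agrees with the follow-up section and the abstract. State in the section on questionnaires whether children also complete the KDQOL-SF. If yearly PedsQL is not intended, the text should instead state and justify an exception for children, and the secondary outcome should be limited to match.

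Marking PedsQL at improvement or deterioration, as for the other questionnaires, would be consistent with those rows but is optional, since the text does not require it.

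The cost is a correction to five cells of Table 1, one clarifying sentence, and one short questionnaire per child per year on the tablet system already built for the cohort.

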### Sample size consideration

Table 2 summarizes the statistical power for time-to-event analyses (minimum detectable hazard ratio [MDHR]). For illustration, MDHRs were described for comparisons between two groups of equal size, which could represent any subgroups of interest (e.g., genetic risk alleles, treatment exposures, and clinical diagnosis). Clinical outcome event rates, including ESRD, death and complete remission, were based on published articles and early observed data in other glomerular disease cohorts [8–11].

**Table 2 Tab2:** Minimum detectable hazard ratio for time-to-event outcomes

Outcome	5-year event rates	MDHR^**a**^ for ***n*** = 3000 (1500/group)
ESRD	0.12	1.36
Death	0.06	1.54
Complete remission of proteinuria (< 0.3 g/day)^b^	0.63–0.97	1.14–1.17

*Abbreviations*: *MDHR* minimum detectable hazard ratio; *ESRD* end-stage renal disease

^a^MDHR is based on the following assumptions: patient follow-up time of 5 years (ESRD and death); a loss of follow-up rate during 5 years hypothesized total of 10%; 80% power, alpha = 0.05

^b^Group sizes for time to complete remission of proteinuria excluded one-third of the group that was in remission at enrolment

### Clinical, patient-oriented outcomes and follow-up

After enrolment, all of the participants will be assessed for whether they reach clinical endpoints each time they visit the outpatient clinic. The clinical endpoints of this study were divided into two categories: 1) deterioration of clinical outcomes was defined by doubling of serum Cr or decrease in estimated glomerular filtration rate (eGFR) by more than 30%, and 2) improvement of clinical outcomes was defined by the remission of glomerulonephritis and proteinuria < 0.3 g/day. Other hard outcomes were defined by ESRD, cardiovascular events, and death. The patients who have proteinuria < 0.3 g/day at baseline have no improvement in clinical outcomes.

Whether the enrolled patients reached each clinical endpoint will be confirmed by the EHR. If the participant displays deterioration, improvement of clinical outcomes, ESRD or cardiovascular events, laboratory findings, urinalysis, and biospecimens, including serum, plasma, buffy coat, and urine, will be collected from the participants. Stools will be collected at baseline only. Additionally, the same information and biospecimens will be collected from the participants at least once per year.

In addition, the patient-oriented outcome will be secured by age-appropriate questionnaires. These outcomes will include symptoms from the patient’s perspective, functional status, nutritional status and health-related quality of life. The questionnaires will be collected every year.

All of the administrative data from Statistics Korea, Health Insurance Review and Assessment Service (HIRA) and National Health Insurance Service (NHIS) and ESRD registry data from the Korean Society of Nephrology will be linked through social security numbers or birth date. However, the information will not be stored by the researchers and will only be used for the collection of clinical outcome information under the approved protocol. The prescribed medication and diagnosis defined by the 10th revision of the International Statistical Classification of Diseases and Related Health Problems (ICD-10) will be collected by HIRA and NHIS. The mortality and the cause of death will be obtained from Statistics Korea data. The reached ESRD outcomes, including dialysis and kidney transplantation, will be determined using the data from NHIS and the Korean ESRD registry from the Korean Society of Nephrology (Fig. 1). For clinical hard outcomes, including death and ESRD, the EHR of each participating centre and various administrative data will be used, so the outcome can be reliably determined even in the case of patient transfer to another hospital or of patients who cannot participate this cohort for other reasons.

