### Electronic health record and questionnaires

The detailed protocol for clinical data and questionnaire collection is described in Table 1. The eligible patients will be evaluated at baseline for demographic information, smoking history, chief complaints, and anthropometric information, including height, weight, and blood pressure. Measurements of the resting blood pressure in the inpatient setting on the kidney biopsy date using an electronic sphygmomanometer will be carried out.

We will collect laboratory findings closest to the kidney biopsy date. Serum creatinine will be measured using an isotope dilution mass spectrometry (IDMS) traceable method. The eGFR will be calculated using the Chronic Kidney Disease Epidemiology Collaboration (CKD-EPI) equation for adults. In children younger than 18 years, the creatinine-cystatin C-based CKiD (Chronic Kidney Disease in Children) equation will be used. Blood laboratory tests, such as complete blood cell count; chemistry, including calcium, phosphorus, total protein, and albumin; lipid panel; electrolyte panel; viral serology, and glomerular disease-related serology will be conducted. Quantitative tests of proteinuria and albuminuria will also be carried out. The information on prescribed medication will include the start and end date of each medication, doses per der day, and total number of prescription days.

The subjects will complete age-appropriate questionnaires concerning the quality of life using Kidney Disease and Quality of Life Short Form (KDQOL-SF) version 1.3, socioeconomic status, educational level, physical activity, health behaviours, health care facility utilization, and nutritional status using semi-food frequency questionnaires (semi-FFQs) and a food diary.

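### Creatinine doubling is not growth-adjusted, so in children it can score deterioration below the plan's own 30% threshold if growth alone raises creatinine by more than about 40%

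*Protocol article*

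**What the plan says.** In the Protocol article, the section Clinical, patient-oriented outcomes and follow-up sets one deterioration rule: "doubling of serum Cr or decrease in estimated glomerular filtration rate (eGFR) by more than 30" percent. The two criteria are joined by OR, and no age limit is attached. The same section says that "all of the participants will be assessed for whether they reach clinical endpoints each time they visit the outpatient clinic".

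Children are among those participants. Study design and population states: "This study will enrol 3000 children (age < 18 years) and adults". It does not say how many will be children.

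Electronic health record and questionnaires separates the ages for eGFR only. For adults: "The eGFR will be calculated using the Chronic Kidney Disease Epidemiology Collaboration (CKD-EPI) equation for adults". For the young: "In children younger than 18 years, the creatinine-cystatin C-based CKiD (Chronic Kidney Disease in Children) equation will be used".

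Table 1 has a row "IDMS-traceable Cr, eGFR", marked at baseline, at years 1 to 5, and in both event columns. Height and weight are marked at baseline, years 1 to 5 and hard outcomes, but not in the column for improvement or deterioration. Deterioration of renal function is a secondary outcome in the Abstract. Reaching it also triggers collection of laboratory data and biospecimens.

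**The concern.** Serum creatinine reflects how much is generated as well as how fast the kidney clears it. A child followed for up to five years gains height and muscle, so creatinine can rise with no change in kidney function. The plan recognises that children need their own eGFR scale, yet leaves the creatinine criterion as a raw ratio to baseline.

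If growth supplies part of the doubling, disease has to supply less of it. A paediatric deterioration event could then stand for a smaller true loss than the same event in an adult. At stake are the comparability of a named secondary outcome across ages and the labelling of samples collected at the event. The Discussion names risk factors for rapid deterioration of renal function as a target for further analysis, so a mislabelled sample in a shared biobank would carry its error into later studies.

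**Working it through.** **The plan's own figures.** The plan gives no figure for the deterioration endpoint. Its only power figures are in Table 2, and they do not involve this rule. As a check, take MDHR = exp(2 × (1.960 + 0.842) / √D), with D = 3000 × event rate × the fraction retained, and alpha read as two-sided.

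| Outcome (5-year rate) | No loss | Half of the 10% loss | Full 10% loss | Table 2 |
|---|---|---|---|---|
| ESRD (0.12) | D = 360: 1.344 | D = 342: 1.354 | D = 324: 1.365 | 1.36 |
| Death (0.06) | D = 180: 1.518 | D = 171: 1.535 | D = 162: 1.553 | 1.54 |

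Table 2 reproduces, and nothing below changes it.

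**Inputs for the deterioration rule.**
- From the document: a creatinine ratio of 2, or an eGFR fall of more than 30%; one rule for all ages; visits to year 5.
- Assumed: creatinine is proportional to generation divided by GFR; eGFR tracks true function; growth alone multiplies creatinine by g between baseline and the event. The document gives no value of g. The range taken is 1.3 to 1.7 over five years, with g = 1.0 at constant body size.

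**Step 1: the creatinine criterion alone.** After a true fractional loss L, the creatinine ratio is g / (1 − L). Setting this to 2 gives L = 1 − g/2.

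**Step 2: the whole rule.** Either criterion is enough, so the rule fires at the smaller of 30% and 1 − g/2.

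| g | True loss at which creatinine doubles | True loss at which the whole rule fires |
|---|---|---|
| 1.0 | 50% | 30% |
| 1.3 | 35% | 30% |
| 1.4 | 30% | 30% |
| 1.5 | 25% | 25% |
| 1.6 | 20% | 20% |
| 1.7 | 15% | 15% |

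**Step 3: the break-even.** 1 − g/2 = 0.30 gives g = 1.4. Below that, the eGFR criterion governs in children as it does in adults. Above it, creatinine doubling governs, and the gap from the adult threshold is 5 points at g = 1.5 and 15 points at g = 1.7.

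**Step 4: timing.** Endpoints are checked at every outpatient visit, so the g that counts is the one accrued by the event. If growth compounds evenly over five years, a five-year factor of 1.5 reaches 1.4 at 5 × ln 1.4 / ln 1.5 = 4.1 years. A factor of 1.7 reaches it at 5 × ln 1.4 / ln 1.7 = 3.2 years. On that assumption only late follow-up is exposed.

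**Step 5: what the criterion contributes.** At constant body size a doubling corresponds to about a 50% loss, which the 30% criterion has already caught. Under these assumptions creatinine doubling adds events only where g exceeds 1.4, and those are events below the plan's own threshold.

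**The case against.** The strongest reply is that the size of the problem rests on g, which has no source in the document, and that the break-even of 1.4 lies inside the assumed range. At g = 1.3 there is no effect. Events before year 5 carry less growth still. This stands, and it is why the point is conditional.

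Three stronger readings are tempting, and the document supports none of them:
- A reader might infer that the rule fires in children at a much smaller loss than in adults, comparing 1 − g/2 with 50%. The 50% figure belongs to the creatinine criterion alone. The adult rule fires at about 30% through eGFR, so that is the right comparator.
- A reader might infer that a child who has merely grown would be scored as deteriorating. That needs 1 − g/2 ≤ 0, so g of at least 2, outside the assumed range. At g = 1.7 a true loss of 15% is still required.
- A reader might say that doubling is always redundant in adults. This follows from the simple proportional model. The article does not give the CKD-EPI coefficients, so it has not been shown for every adult.

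It can also be said that a condensed article may leave paediatric detail to the full protocol. That carries limited weight here. The article states the rule for all participants, and where it wanted an age distinction, for eGFR, it made one. Finally, creatinine is stored at annual and event visits and height at annual ones, so later users could re-score. That softens the harm, but it does not correct the event label or the trigger for sampling.

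**Conclusion.** The creatinine-doubling criterion applies to children without growth adjustment, and this is a real but conditional weakness in a secondary outcome. For growth factors up to 1.4, children and adults are both scored at about 30% true loss. Above 1.4 the rule fires in children below that threshold, at 25% for g = 1.5 and 15% for g = 1.7. Some paediatric deterioration events, and the samples they trigger, would then reflect a smaller true loss than in adults.

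This rests on the assumed g, on creatinine being proportional to generation over GFR, and on the eGFR criterion working as specified. On the last, Table 1 does not list cystatin C, which the named paediatric equation needs. If it is not measured, doubling alone would operate in children, and for g below 1.4 they would be scored later than adults rather than earlier. That is a separate matter to reconcile. No event count is possible because the paediatric share is not stated. The primary outcomes, mortality and ESRD, and Table 2 are unaffected.

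**What to change.** For participants under 18 at baseline, define deterioration by the eGFR criterion alone (a fall of more than 30%, using the paediatric body-size-adjusted equation) and drop raw creatinine doubling. Leave the adult definition as it is. This is a short change to the endpoint definition in Clinical, patient-oriented outcomes and follow-up.

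Little sensitivity should be lost, because a true halving of function already exceeds the 30% criterion. There are two costs. The wording then differs by age. Height must also be available when deterioration is assessed, and Table 1 does not mark it in that column, so the mark should be added or the plan should state that the latest recorded height is used. The change also relies on the paediatric eGFR being computable at those visits, so the cystatin C gap in Table 1 should be settled alongside it. Replacing the paediatric equation is not needed for this point.
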